### I (intervention)

All patients will receive the examinations of Sonazoid-CEUS, conventional ultrasound and contrast-enhanced MRI (CEMRI), and 65 of them should have additional CECT scans.

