### C (comparison or control)

Kupffer phase whole liver scan for metastases (KPWLSM) is a self-control, blind map-reading, single-center, prospective superiority trial. We set Sonazoid-CEUS, and CECT as the test group, and conventional ultrasound as the control group.

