#### Secondary endpoint

The secondary endpoint is the comparative analysis of diagnostic accuracy between Sonazoid-CEUS and CECT in a single lesion. When the results show that Sonazoid-CEUS provide better diagnostic efficacy than CECT, the study will be considered to be successful because it means the data collected in the present Sonazoid-CEUS could be a potential diagnostic tool instead of CECT despite the good diagnostic performances achieved by the latter.

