### Data analysis

A commercially available software package (SAS version 9.2, SAS Analytics, Marlow, UK) will be used for all the statistical analysis, and the significance level was 0.05 for two-sided tests. Descriptive data will be mainly used in the study. Efficacy analyses of sensitivity, specificity, positive predictive value, negative predictive value and accuracy will be performed using the efficacy population including subjects who received Sonazoid-CEUS, conventional ultrasound, CECT and CEMRI in screening liver metastases.

For the comparison of superiority among Sonazoid-CEUS, conventional ultrasound and CECT, intra-individual comparison will be made in terms of the detection rate of the number of detected liver metastatic lesions with pared-samples *T*-test. And the Chi-square test or Fisher exact test will be used to compare the diagnostic accuracy of the three imaging modalities in screening liver metastases.

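### Diagnostic accuracy of modalities read in the same patients is to be compared with chi-square or Fisher tests for independent groups; the secondary endpoint needs a paired test

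*Protocol article*

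**What the plan says.** Under C (comparison or control), the Protocol article calls the study a "self-control, blind map-reading, single-center, prospective superiority trial". The intervention paragraph sets out who has which examination as follows: "All patients will receive the examinations of Sonazoid-CEUS, conventional ultrasound and contrast-enhanced MRI (CEMRI), and 65 of them should have additional CECT scans". The modalities are therefore read in the same people.

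The Data analysis section treats its two comparisons differently. For lesion counts, "intra-individual comparison will be made in terms of the detection rate of the number of detected liver metastatic lesions", with a paired t-test. For accuracy, "the Chi-square test or Fisher exact test will be used to compare the diagnostic accuracy of the three imaging modalities in screening liver metastases". Sensitivity, specificity, predictive values and accuracy are to be computed "using the efficacy population including subjects who received Sonazoid-CEUS, conventional ultrasound, CECT and CEMRI".

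The secondary endpoint is the "comparative analysis of diagnostic accuracy between Sonazoid-CEUS and CECT in a single lesion". The Secondary endpoint section gives it its own success criterion: the study succeeds if CEUS shows better diagnostic efficacy than CECT. The Sample size section sizes the study for both superiority and diagnostic accuracy, using a paired non-parametric test. No McNemar, Cochran Q or other paired method for accuracy is named anywhere.

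**The concern.** The Pearson chi-square and Fisher tests take the variance of a difference between two proportions as the sum of two independent variances. When both proportions come from the same patients, that variance omits the covariance. A lesion that is hard to see on one modality tends to be hard on the other, so correct calls should be positively correlated. The variance used is then too large, the p-value too large and the test too weak.

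At stake is the secondary endpoint, which carries a success claim and rests on the smaller CECT subset, where there is little power to give away. The planned analysis of accuracy also differs from the kind of test on which the sample size was based.

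**Working it through.** **The plan's own figures.** 330 and 65 cannot be uniquely reproduced: the inputs are ranges, power is given as 80% or 90%, and no between-modality correlation is stated. Paired sensitivity calculations over those ranges span 54 to 1885 subjects after dropout. Single combinations do match: sensitivity 0.625 versus 0.84, prevalence 25%, 90% power and phi 0.2 give 329; AUC 0.75 versus 0.95, prevalence 50%, 80% power and correlation 0 give 65. The figures are neither confirmed nor refuted, and this point does not depend on them.

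**Inputs from the Sample size and Data analysis sections.**
- Two-sided alpha 0.05.
- After 10% dropout: 330 × 0.9 = 297, and 65 × 0.9 = 58.5, taken as 58.
- Prevalence 25–50%: 297 × 0.50 ≈ 148 and 297 × 0.25 ≈ 74 diseased patients.
- Mid-range sensitivities: ultrasound (62.5 + 87.7)/2 = 75.1%; CEUS (73 + 95)/2 = 84%. CECT sensitivity 90%.

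**Assumptions.** The correlation phi is varied from 0 to 0.5. Accuracies of 75% and 90% in the CECT subset are illustrative.

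**True size.** With equal proportions p and q = 1 − p, the paired difference has variance 2pq(1 − phi)/n, while chi-square uses 2pq/n. Hence size = 2[1 − Φ(1.96/√(1 − phi))].
- phi 0: 5.0%
- phi 0.2: 2.8%
- phi 0.3: 1.9%
- phi 0.5: 0.6%

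Simulation with 148 patients and both sensitivities 0.75 gave 5.0%, 2.8%, 1.8% and 0.6% for chi-square, with Fisher lower still (3.9%, 1.9%, 0.9%, 0.3%). McNemar stayed at 4.8–5.3%.

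**Power.** Let p11 = p1p2 + phi·√(p1q1p2q2), p10 = p1 − p11, p01 = p2 − p11, ψ = p10 + p01 and d = p1 − p2. The estimate has standard deviation σ = √((ψ − d²)/n). Chi-square needs a difference above 1.96·√(2p̄q̄/n); McNemar needs one above 1.96·√(ψ/n). Power = Φ((d − threshold)/σ).

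Example, n = 148, 0.84 versus 0.751, phi 0.5: p11 = 0.7101, p10 = 0.1299, p01 = 0.0409, ψ = 0.1708, d = 0.089, σ = 0.0332.
- Chi-square: threshold 1.96 × 0.0469 = 0.0919; power 46.5%.
- McNemar: threshold 1.96 × 0.0340 = 0.0666; power 75.0%.

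| Comparison | n | phi | Chi-square | McNemar |
|---|---|---|---|---|
| CEUS–ultrasound sensitivity, 84% vs 75.1% | 148 | 0.2 | 47% | 56% |
| same | 148 | 0.5 | 47% | 75% |
| same | 74 | 0.2 | 24% | 32% |
| same | 74 | 0.5 | 19% | 46% |
| CECT subset, accuracy 75% vs 90% | 58 | 0.3 | 58% | 69% |
| same | 58 | 0.5 | 59% | 81% |
| CEUS–CECT sensitivity, 84% vs 90% | 58 | 0.5 | 8% | 26% |
| same, half diseased | 29 | 0.5 | 4% | 15% |

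These are normal approximations. Simulation of the 58-patient accuracy case gave 60% versus 71% at phi 0.3 and 61% versus 88% at phi 0.5. Exact McNemar against Fisher gave 63% versus 47% and 78% versus 45%.

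**A single data set.** Take 148 diseased patients: 105 positive on both, 20 on CEUS only, 8 on ultrasound only, 15 on neither. The margins are 125/148 and 113/148. Chi-square gives p = 0.079 and Fisher p = 0.107. McNemar gives (20 − 8)²/28 = 5.14, p = 0.023 (exact 0.036). The conclusion at 0.05 reverses.

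**The case against.** **Chi-square might mean McNemar's chi-square.** In a condensed article this is possible but weak. Fisher's test is named as the alternative, and it is the small-sample companion of the independent-groups test. The within-patient wording is used only for lesion counts. If McNemar was meant, the text still needs correcting.

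**The error is conservative.** This stands. Under positive correlation the planned tests do not produce spurious success; they miss real differences. At phi 0 nothing is lost. Only negative correlation would inflate the size (simulated 6.4% at phi −0.15), and that is not expected here.

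**A paired test does not rescue the CECT comparison.** This also stands. At 84% versus 90% sensitivity, power is at most about 26% with either test, even if all 58 patients were diseased.

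**Stronger readings that the document does not support.**
- A reader might infer that the power of the whole self-controlled design is thrown away. The primary lesion-count comparison is paired, so it is not.
- A reader might infer that about 297 CEUS and ultrasound results would be set against about 58 CECT results. The efficacy population is described as subjects who received all the modalities, which makes the comparison fully paired. The imbalance arises only if CECT is not required for that population, and independent-groups tests would then still be wrong because the samples overlap.
- A reader might infer that clustering of lesions inflates the error rate. The secondary endpoint concerns a single lesion, and neither the size nor the net direction of a clustering effect can be derived from the document.

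**Conclusion.** The concern holds for the accuracy comparisons, including the secondary endpoint, and not for the primary endpoint. The named tests contradict the self-control design and the paired test behind the sample size. Because the article names a test, this is not a detail left to an analysis plan.

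In size, the true error rate is about 0.6–1.9% instead of 5% for phi between 0.5 and 0.3. The loss of power is about 8 to 28 percentage points in the CEUS–ultrasound sensitivity examples (phi 0.2 to 0.5, prevalence 25–50%), and about 11 to 22 points in the illustrative CECT accuracy example (phi 0.3 to 0.5).

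All of this rests on the assumed phi. The examples with 148 and 74 patients also assume that CEUS–ultrasound accuracy is analysed in all 297 completers; if CECT is required, the numbers are smaller.

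**What to change.** In Data analysis, replace the chi-square/Fisher sentence as follows.
- Compare sensitivity, specificity and accuracy with McNemar's test (exact if discordant pairs are few) and report the paired difference with a 95% confidence interval.
- Do this separately for CEUS–ultrasound and for CEUS–CECT, the latter in patients who had both, and state which patients enter each comparison.
- Use a paired predictive-value method for PPV and NPV; McNemar's test does not compare these.
- If more than one lesion per patient is analysed, use GEE or a bootstrap that resamples patients.

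The cost is a few sentences and a few lines of code, with no new data or patients. The change should be made before the data are analysed. It will not by itself give the CEUS–CECT sensitivity comparison adequate power.

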#### Sample size

As sample size calculation is closely related to research design, and this study consists of several parts which involves the comparison of superiority and diagnostic accuracy, so the calculation of multiple sample sizes is carried out, followed by the larger size as the final calculation results.

For the comparison of superiority and diagnostic accuracy between conventional ultrasound and Sonazoid-CEUS, we assumed a 25–50% prevalence of liver metastatic lesions in our target population (17), while 62.5–87.7% of sensitivity, 40–60% of specificity in conventional ultrasound (12), and 73–95% of sensitivity, 65–75% of specificity in Sonazoid-CEUS according to previous literature studies (18, 19). Also, a 10% dropout rate is included, and the required number of subjects is calculated to be 330.

For the comparison of superiority and diagnostic accuracy between CECT and Sonazoid-CEUS, we also assumed a 25–50% prevalence of liver metastatic lesions in our target population, while 90% of sensitivity in CECT (19), and 73–95% of in Sonazoid-CEUS according to previous literature studies. Since no AUC has been reported, this study attempted to use AUC of 0.75, 0.85, 0.95 for sample size calculation, and a 10% dropout rate is included. The required number of subjects for this part is calculated to be 65.

The sample size was calculated on the non-parametric module of PASS software using paired non-parametric test. With all these assumptions, a minimum of 330 patients are needed to obtain 80% or 90% statistical power for non-parametric test with an α equal to 0.05, of which at least 65 cases need to have received CECT.

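### The accuracy comparison that alone can make the secondary endpoint a success against CECT could favour Sonazoid-CEUS despite lower sensitivity, and no comparison of sensitivity or specificity is named

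*Protocol article*

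**What the plan says.** The Data analysis section of the protocol article lists sensitivity, specificity, positive and negative predictive value and accuracy as separate efficacy analyses. It then names two comparative tests. One is a within-patient paired t-test on the number of detected metastatic lesions, which serves the primary endpoint. The other is for accuracy: "the Chi-square test or Fisher exact test will be used to compare the diagnostic accuracy of the three imaging modalities in screening liver metastases". No comparison is named for sensitivity or for specificity.

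The Secondary endpoint section defines the endpoint as diagnostic accuracy of Sonazoid-CEUS against CECT in a single lesion. Its success rule is: "When the results show that Sonazoid-CEUS provide better diagnostic efficacy than CECT, the study will be considered to be successful". The rule goes on to present Sonazoid-CEUS as a possible replacement for CECT. It sets no condition on sensitivity and none on the primary result.

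The Sample size section gives the planning values. On prevalence: "we assumed a 25–50% prevalence of liver metastatic lesions in our target population (17". For the CECT comparison: "90% of sensitivity in CECT (19), and 73–95% of in Sonazoid-CEUS according to previous literature studies". The specificity of Sonazoid-CEUS is put at 65–75%. No specificity is given for CECT.

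**The concern.** The trial asks whether Sonazoid-CEUS finds metastases well enough to spare patients a CT. For that question a missed metastasis and a false alarm are different errors, but the proportion correct counts them equally and weights them by how many patients or lesions happen to be positive. A test with fewer false alarms can therefore have the higher accuracy while it misses more disease. Its lead also depends on the case mix recruited and not only on the tests.

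Lower sensitivity than CECT lies inside the planning assumptions, since the Sonazoid-CEUS range starts at 73% and CECT is put at 90%. At stake is the secondary claim that Sonazoid-CEUS could stand in for CECT, which could be made without any comparison of how many metastases each modality misses.

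**Working it through.** **Inputs (Sample size section).** Prevalence *p* = 0.25 to 0.50. Sensitivity: CECT 0.90, Sonazoid-CEUS 0.73 to 0.95. Specificity: Sonazoid-CEUS 0.65 to 0.75, CECT not stated. CECT subset 65 with 10% dropout: 65 × 0.90 = 58.5, taken as 58 evaluable. Two-sided α = 0.05 (Data analysis).

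**The plan's own figure.** The 65 cannot be reconstructed from the text: the inputs are ranges, three AUC values are offered, power is 80% or 90%, and no correlation between paired readings is given. Some combinations reach it (for example AUC 0.75 against 0.95, prevalence 50%, 80% power and an assumed correlation of 0.3), but the text identifies none. The point does not depend on this.

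**Step 1: the weights.** Accuracy = *p* × sensitivity + (1 − *p*) × specificity. The weight on specificity is 1 − 0.25 = 75% at the lower prevalence and 1 − 0.50 = 50% at the upper.

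**Step 2: the break-even against CECT.** A sensitivity loss of 0.90 − 0.73 = 0.17 is offset by a specificity gain of 0.17 × *p* / (1 − *p*):
- *p* = 0.25: 0.17 × 0.25 / 0.75 = 0.057, or 5.7 points.
- *p* = 0.50: 0.17 × 0.50 / 0.50 = 0.17, or 17 points.

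**Step 3: how likely a significant reversal is.** This needs a CECT specificity, which is an assumption here, shown over 0.40 to 0.70. Sonazoid-CEUS is set at its lowest sensitivity (0.73) and highest specificity (0.75), the corner that best produces the reversal. Its accuracy is 0.25 × 0.73 + 0.75 × 0.75 = 0.745 at 25% prevalence and 0.50 × 0.73 + 0.50 × 0.75 = 0.740 at 50%. Power is for the planned unpaired chi-square test with 58 readings per modality.

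| Prevalence | Assumed CECT specificity | CECT accuracy | Sonazoid-CEUS accuracy | Power to show Sonazoid-CEUS better |
|---|---|---|---|---|
| 25% | 0.40 | 0.525 | 0.745 | 70% |
| 25% | 0.50 | 0.600 | 0.745 | 38% |
| 25% | 0.60 | 0.675 | 0.745 | 13% |
| 25% | 0.70 | 0.750 | 0.745 | not higher |
| 50% | 0.40 | 0.650 | 0.740 | 18% |
| 50% | 0.50 | 0.700 | 0.740 | 7% |
| 50% | 0.60 | 0.750 | 0.740 | not higher |
| 50% | 0.70 | 0.800 | 0.740 | not higher |

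A high chance of a misleading win needs low prevalence, a very low CECT specificity and the corner values for Sonazoid-CEUS all at once.

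**Step 4: what a direct test of sensitivity could show.** Reference-positive patients in the subset: 58 × 0.25 = 14.5 to 58 × 0.50 = 29. For a McNemar test with readings assumed conditionally independent, ψ is the sum of the two discordant probabilities and *d* their difference, and power = Φ[(*d*√*n* − 1.96√ψ) / √(ψ − *d*²)]. For 0.90 against 0.95, the discordant probabilities are 0.90 × 0.05 = 0.045 and 0.95 × 0.10 = 0.095, so ψ = 0.14 and *d* = 0.05. Power is 7% at *n* = 14.5 and 11% at *n* = 29. For a true fall from 0.90 to 0.73, the same formula gives 20% and 36%.

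**The case against.** **The primary test already looks at missed metastases.** This stands. A reader might infer that accuracy is the only planned test of diagnostic performance, so that the trial as a whole could declare Sonazoid-CEUS better while it misses more metastases. The documents do not support that. The paired t-test compares detected metastatic lesions, and the Primary endpoint section requires Sonazoid-CEUS to detect more than both comparators. The weakness is confined to the secondary route to success, which is not conditional on the primary.

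**Diagnostic accuracy may be an umbrella term.** The Sample size section pairs that term with sensitivity, specificity and AUC ("this study attempted to use AUC of 0.75, 0.85, 0.95 for sample size calculation, and a 10% dropout rate is included"), and the success rule speaks of efficacy, a word that Data analysis applies to all five measures. This is a fair reading, and a separate analysis plan may name further tests. But Data analysis lists accuracy as its own measure beside sensitivity and specificity, and the success rule does not say which measure decides. Under the umbrella reading the rule is ambiguous, and the same edit resolves it.

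**The unit differs.** This stands for the numbers. The 50–75% weight is at patient level, while the secondary endpoint concerns a single lesion. There *p* becomes the share of assessed lesions that are metastatic, which is not stated; the higher that share, the larger the specificity gain needed to offset a loss of sensitivity. The dependence on case mix remains.

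**A dramatic example is easy to build against conventional ultrasound.** At 25% prevalence, Sonazoid-CEUS at 73% sensitivity and 75% specificity has accuracy 74.5%, against 0.25 × 0.877 + 0.75 × 0.40 = 51.9% for ultrasound at 87.7% and 40%. A reader might take the 22.6-point gap as the size of the problem. It pairs opposite corners of the ranges, and conventional ultrasound is not part of the secondary success rule. At the midpoints Sonazoid-CEUS has the higher sensitivity (84% against 75.1%), so no conflict arises.

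**Conclusion.** The point holds for the secondary endpoint only. As written, the plan can call Sonazoid-CEUS better than CECT on accuracy with no named comparison of sensitivity, and its own planning values leave room for that to coincide with lower sensitivity. The break-even specificity gain is 5.7 points at 25% prevalence and 17 points at 50%, and the plan cannot exclude such a gain because it assumes no CECT specificity.

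This rests on reading accuracy as the proportion correct, on patient-level prevalence standing in for the unknown lesion mix, and on the low end of the Sonazoid-CEUS sensitivity range. With about 58 evaluable CECT patients, a statistically significant misleading result is possible but not likely. The primary claim on lesion counts is untouched.

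**What to change.** In Data analysis, compare Sonazoid-CEUS with CECT separately on sensitivity (reference-positive) and specificity (reference-negative), within patient, each as a paired difference with a 95% CI. Keep accuracy and the predictive values as descriptive figures. In Secondary endpoint, say what diagnostic efficacy means, and make no claim that Sonazoid-CEUS can replace CECT on accuracy alone without the sensitivity difference and its CI reported beside it.

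This changes wording only and needs no new data. The cost is precision: with roughly 14–29 reference-positive CECT patients the sensitivity interval will be wide, and a formal superiority test has little power (7–11% for 90% against 95%). Sensitivity superiority should therefore not become a new pass-or-fail rule at this sample size. The CECT comparison is better presented as estimation.

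### The only accuracy test described covers three modalities and does not name the Sonazoid-CEUS versus CECT single-lesion comparison that decides the secondary endpoint

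*Protocol article*

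**What the plan says.** The protocol article gives the secondary endpoint in the same words under Design (O, outcome) and under Secondary endpoint: "The secondary endpoint is the comparative analysis of diagnostic accuracy between Sonazoid-CEUS and CECT in a single lesion". The Secondary endpoint section adds a directional success rule: "When the results show that Sonazoid-CEUS provide better diagnostic efficacy than CECT, the study will be considered to be successful".

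Sample size treats this pair as a contrast of its own. It has separate assumptions (CECT sensitivity 90%, AUC values of 0.75, 0.85 and 0.95) and a separate requirement of 65 patients.

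Data analysis contains one sentence on testing accuracy: a chi-square or Fisher exact test "will be used to compare the diagnostic accuracy of the three imaging modalities in screening liver metastases". For the level it says that "the significance level was 0.05 for two-sided tests". It defines the efficacy population as subjects who had all four examinations.

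**The concern.** The endpoint and the test do not line up. The endpoint is a two-modality contrast on a lesion. The test is described for three modalities and mentions no lesion. Conventional ultrasound, which has no part in the secondary question, enters the only accuracy test available to answer it.

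A single test across three groups rejects when any one of them differs. By the plan's own assumptions ultrasound is generally the weakest of the three. A significant three-way p-value beside a numerically higher CEUS accuracy could then be taken as meeting the success rule against CECT, although the weakness of ultrasound produced the significance. At stake is a declared claim of success: that CEUS could replace CECT as a diagnostic tool.

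**Working it through.** **Step 1. Endpoint and test side by side.**

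| | Secondary endpoint | Accuracy test in Data analysis |
|---|---|---|
| Contrast | Sonazoid-CEUS versus CECT | three modalities, including conventional ultrasound |
| Unit | a single lesion | not stated; only the screening setting is given |
| Decision | CEUS better than CECT | two-sided chi-square or Fisher exact at 0.05 |

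No sentence in Data analysis names the CEUS-CECT pair for accuracy. The article gives no operating characteristic for this test, so there is no figure of the plan's own to reproduce on this point.

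**Step 2. Inputs for the consequence under a single three-way test.** From Sample size:
- Prevalence: "we assumed a 25–50% prevalence of liver metastatic lesions in our target population". Both ends, 25% and 50%, are used.
- Conventional ultrasound: "62.5–87.7% of sensitivity, 40–60% of specificity in conventional ultrasound". Mid-range values are about 75% and 50%.
- Sonazoid-CEUS: sensitivity 73–95% and specificity 65–75%. Mid-range values are 84% and 70%.
- 65 patients with CECT, hence 65 readings per modality in a population that had every examination.

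Assumptions that are not in the article:
- CECT accuracy is set by assumption, because no CECT specificity is given.
- Readings are treated as independent, as an ordinary chi-square test does.

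**Step 3. Accuracy = prevalence × sensitivity + (1 − prevalence) × specificity.**
- 25% prevalence: ultrasound 0.25 × 0.75 + 0.75 × 0.50 = 0.5625; CEUS 0.25 × 0.84 + 0.75 × 0.70 = 0.735.
- 50% prevalence: ultrasound 0.50 × 0.75 + 0.50 × 0.50 = 0.625; CEUS 0.50 × 0.84 + 0.50 × 0.70 = 0.77.

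**Step 4. Three-way rejection probability with CECT equal to CEUS.** The noncentrality is λ = n Σ(pᵢ − p̄)² / [p̄(1 − p̄)], with 2 degrees of freedom.
- 25% prevalence: p̄ = (0.5625 + 0.735 + 0.735)/3 = 0.6775. λ = 65 × (0.1150² + 2 × 0.0575²)/(0.6775 × 0.3225) = 5.90. Rejection is about 58%.
- 50% prevalence: p̄ = (0.625 + 0.77 + 0.77)/3 = 0.7217. λ = 65 × (0.0967² + 2 × 0.0483²)/(0.7217 × 0.2783) = 4.54. Rejection is about 46%.

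Simulation agrees. A direct two-group test of CEUS against CECT rejects in about 5%.

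**Step 5. The event that matters.** The success rule also needs CEUS to come out ahead of CECT, so the relevant event is a significant test with CEUS numerically higher. Simulated rates with 65 readings per modality:

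| Truth | Prevalence | Three-way test significant | Significant and CEUS ahead | Direct test significant and CEUS ahead |
|---|---|---|---|---|
| CEUS = CECT | 25% | 58% | 27% | 2.5% |
| CEUS = CECT | 50% | 46% | 21% | 2.5% |
| CECT 5 points better | 25% | 74% | 15% | 0.4% |
| CECT 5 points better | 50% | 64% | 12% | 0.4% |

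**Step 6. Sensitivity to inputs.**
- With CECT equal to CEUS and 65 readings per modality, three-way rejection runs from about 5% to over 99% across the stated sensitivity and specificity ranges.
- After the 10% dropout (59 readings per modality), the mid-range figures are about 53% and 42%.
- If all 330 ultrasound and CEUS readings were set against 65 CECT readings, they would be about 98–99%.

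**The case against.** The strongest reply is that Data analysis never says one three-way test will be run. The preceding sentence plans a comparison among the same three modalities by paired t-test, which can take only two at a time. Sample size handles CEUS against ultrasound and CEUS against CECT as separate contrasts, and the success rule is itself pairwise. Pairwise chi-square or Fisher tests are therefore a plausible intention, and a CEUS-CECT test would then exist. This stands: under that reading none of the rates above apply. What remains is that the text does not say so and does not identify which comparison decides the secondary endpoint.

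A reader might infer that the analysis uses a different unit from the endpoint, a screening result in place of a lesion. The documents do not support that. The article uses the screening phrase as a general description of the setting and attaches it to the primary endpoint too, which counts lesions. The unit is unspecified in the test sentence, not contradicted.

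A reader might also take the total rejection rates of 46–74% as the risk of a false claim of success. They are not. Success requires CEUS to be better than CECT, and nothing in the article lets a three-way p-value alone settle that. The joint rates of 12–27% are the relevant ones, and they still require the three-way p-value to be used as the evidence for the pair.

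Finally, a condensed article may leave follow-up tests and intervals to the full protocol or SAP. That is fair for those details. It does not cover an accuracy test that the article does state and that does not match the endpoint it should serve.

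**Conclusion.** The point holds as a mismatch in the current text. The secondary endpoint has a defined pair, a defined unit, its own sample size and its own success rule, and the only accuracy test stated names neither the pair nor the unit. Followed literally, that test does not answer the secondary question.

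The size is conditional. It assumes one three-way test, mid-range inputs, an assumed CECT accuracy and independent readings at 65 per modality. If CEUS and CECT are then equally accurate, a significant result with CEUS ahead arises in about 21–27% of trials, roughly 8 to 11 times the 2.5% of a direct test (21/2.5 = 8.4; 27/2.5 = 10.8). If CECT is 5 points better it still arises in about 12–15%, against 0.4%. The documents do not establish that the three-way reading is the intended one, so these figures show what the wording permits and are not the trial's error rate. The matter is worth correcting because a success claim hangs on it.

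**What to change.** In Data analysis, state that the secondary endpoint is decided by a direct within-patient comparison of Sonazoid-CEUS with CECT on the single lesion of the Secondary endpoint section, in patients who had both scans. Use a paired method (McNemar's test, for example), since both readings come from the same patient, and report the accuracy difference with its 95% confidence interval. Add that any accuracy comparison across all three modalities is supportive and does not decide the secondary endpoint.

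The cost is a change of analysis wording and one pairwise analysis on data already being collected. No extra patients or examinations are needed.
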